### Statistical analysis

We will be following the recently published extension to Consolidated Standards of Reporting Trials (CONSORT)^35^ when reporting the results of this feasibility trial. As this is a feasibility study there is no formal sample size calculation. Seventy participants were considered a large enough sample to consider the practicalities of recruitment and delivering the intervention.

For this feasibility study, we will calculate and present in a CONSORT flow chart:the proportion of adults with ASD consenting to the study;the proportion completing the baseline assessment and entering the randomised phase;for those in the intervention group, the number of guided self-help sessions attended and the proportion completing five or more sessions;the proportion completing follow-up assessments at 10, 16 and 24 weeks postrandomisation.

We will explore the sensitivity to change of the various self-reported measures of depression in comparison with the GRID-HAMD (clinician-rated assessment of depression) in order to identify the most appropriate outcome measures for the main trial. We will also compare the continuous scores on the depression outcome measures between groups. The SD of the chosen primary outcome will inform the sample size calculation for the large-scale RCT.

We will evaluate the service use and economical evaluation questionnaire by examining the rates of completion across individual questions. We will compare the information provided by participants about primary and secondary care health service use with information gathered from GP and secondary care records.

### Qualitative study

In-depth interviews will be conducted with participants (from both arms of the trial) 10 weeks after randomisation (after 10 week outcome measurement is complete). These interviews will consider and compare views and experiences of the trial and the acceptability of the guided self-help intervention. All therapists delivering the intervention will also be interviewed towards the end of the trial to illuminate the perceived effectiveness and acceptability of treatments and explore any barriers to its uptake outside of the trial.

Purposive sampling will select interviewees in order to attempt to capture maximum variation in views and experiences in order that they adequately reflect those of a range of participants. All participants in the trial will be asked if they are willing to be contacted about taking part in a qualitative interview at the time of trial consent. From participants who indicate that they are willing to be contacted, a purposive sample will be drawn in relation to (1) the trial site, (2) arm of the trial and (3) sociodemographic variables such as age, gender, ethnicity and socioeconomic status (with participants being selected from areas of high and low social–economic deprivation, based on Index of Multiple Deprivation (IMD 2007) score.^36^ Interviews will be analysed in batches, and sampling will continue until no new themes are emerging from the interviews. This is likely to include up to 24 participants as well as two to three therapist interviews.

All interviews will be conducted by telephone or face-to-face in a location of the participants’ choice. At interview, a flexible topic guide will be used to ensure primary issues are covered during all interviews, but without dictating data collection, allowing participants to introduce unanticipated issues. Interviews are expected to last between 45–60 min. With informed consent, interviews will be recorded using a digital voice recorder, transcribed and anonymised.

Interview transcripts will be checked for accuracy and then imported into NVivo10 qualitative data analysis software,^37^ to aid management and indexing of data. Thematic analysis^38^ using a data-driven inductive approach^39^ will be used to scrutinise the data in order to identify and analyse patterns and themes of particular salience for participants and across the dataset using constant comparison techniques.^40^ Analysis will begin shortly after data collection starts, will be ongoing and iterative. Analysis will inform further data collection; for instance, analytical insights from data gathered in earlier interviews will help identify any changes that need to be made to the topic guide during later interviews. Transcripts from the participants and therapists’ interviews will be analysed separately, with coding frames being developed for each. A subset of transcripts will be independently double-coded by other members of the research team and compared. Discrepancies will be discussed and resolved to achieve a coding consensus.

### Monitoring and adverse events

Adverse events and risk standardised operating procedures have been developed and will be followed by all researchers and therapists working on the trial. Adverse events are defined as significant negative episodes, or significant deterioration in condition, which happen to participants during their time in the trial. These will be reported by research assistants and trial therapists to senior trial staff, who will ascertain whether these are thought to be linked to participation in the trial, and keep records of each event on an adverse events database. All serious adverse events of an unexpected and unrelated nature will be reported to the main Research Ethics Committee, the study Sponsor and Trial Steering Committee (TSC). Suicide risk will be monitored using the suicidality items on the PHQ-9 and BDI-II which are administered at baseline, and 10, 16 and 24-week follow-up. If the participant states that they have had suicidal/self-harming thoughts every day in the last week (PHQ-9) or that they would like to kill themselves, or would kill themselves if they had chance (BDI-II), then a letter will be sent to their GP highlighting the individual’s risk. If the individual is considered to be high risk, a qualified clinician may also follow-up by offering information to the participant regarding local crisis teams, and call the GP to ensure the information is shared in a timely manner.

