### Independent oversight

A TSC and Data Monitoring and Ethics Committee will have independent oversight of the study, meeting at 6 monthly intervals with quarterly reports of adverse and serious adverse events.

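### The serious adverse event rule reports events judged unrelated to the trial and leaves out those judged related

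*Protocol article*

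**What the plan says.** Under Monitoring and adverse events, the protocol article sets out two steps.

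1. Research assistants and therapists report adverse events to senior trial staff, "who will ascertain whether these are thought to be linked to participation in the trial" and who "keep records of each event on an adverse events database".
2. The next sentence says which serious events leave the trial team: "All serious adverse events of an unexpected and unrelated nature will be reported to the main Research Ethics Committee". The Sponsor and the TSC are named as the other recipients.

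The same section opens by noting that "Adverse events and risk standardised operating procedures have been developed". The content of those procedures is not given.

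Under Independent oversight, the TSC and the Data Monitoring and Ethics Committee (DMEC) oversee the study, "meeting at 6 monthly intervals with quarterly reports of adverse and serious adverse events". That sentence has no filter on relatedness. It names neither the Research Ethics Committee nor the Sponsor.

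**The concern.** A relatedness judgement made just before a reporting rule would normally pick out events that the trial may have caused. Here it does the opposite: a finding that the trial contributed to an unexpected serious event takes that event out of the rule, and a finding of no link puts it in. The article gives no reason for this, and none is apparent.

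The stake is participant safety. The trial randomises depressed adults with PHQ-9 scores from 10 to 27 and monitors suicidality. The intervention is newly developed and is delivered by therapist guides who are not qualified psychologists. Serious events linked to the trial are the ones most likely to call for a change in its conduct, and the stated rule does not send them promptly to any body outside the trial team. The section on trial status says recruitment was open, so the rule applied to participants already enrolled.

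**Working it through.** The documents give no figure to reproduce, and no sample size, error rate or event rate enters. The check is to apply the sentence to every kind of serious adverse event (SAE) and then to look for another route in the rest of the article.

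**Inputs**
- Event-level rule (Monitoring and adverse events): report if serious AND unexpected AND unrelated. Recipients: Research Ethics Committee, Sponsor, TSC.
- Relatedness judgement (same section): made by senior trial staff.
- Internal record (same section): every event goes on the database, whatever its relatedness.
- Periodic route (Independent oversight): quarterly reports of adverse and serious adverse events under the TSC and DMEC, whatever their relatedness.

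**Result for the four kinds of SAE**

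| SAE | Event-level rule (ethics committee, Sponsor, TSC) | Quarterly reports (TSC, DMEC) | Any stated route to the ethics committee or Sponsor |
|---|---|---|---|
| Unexpected, unrelated | covered | yes | yes |
| Unexpected, related | not covered | yes | none |
| Expected, related | not covered | yes | none |
| Expected, unrelated | not covered | yes | none |

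The rule covers 1 of 4 kinds of SAE and 0 of the 2 related kinds. If unrelated is replaced by related, the covered cell moves to the second row, which is where the preceding relatedness judgement points.

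**Length of the gap**
- TSC and DMEC: four reports a year means an interval of 12/4 = 3 months, or 52/4 = 13 weeks. A related SAE could therefore wait up to about 3 months to be reported. That is longer than the 10-week intervention, so one participant's whole course of treatment can fall between two reports.
- Research Ethics Committee and Sponsor: the quarterly reports are not said to go to them, so no waiting time can be calculated. The article states no route.
- The article sets no time limit for event-level reporting, so the 3 months is the longest wait under the periodic route and not an extra delay over a stated standard.

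**The case against.** The strongest reply is that this is a drafting slip in a condensed article. Separate operating procedures exist and are to be followed by all staff, and a full protocol is cited. Either may state the rule correctly, so no actual failure to report has been shown. This stands as a limit on what can be claimed about conduct. It does not rescue the sentence: the article does not leave the rule to another document, but states it, and states it wrongly. If the operating procedures differ, the public protocol contradicts them.

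A second reply is that the sentence says which events will be reported and does not forbid reporting others. That is true as a matter of wording. But it is the only sentence that defines what goes to the ethics committee and the Sponsor, so a reader following it has no instruction to send them a related event.

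A third reply is that related events still reach independent oversight through the quarterly reports, and that the relatedness judgement has some use there and in the database. This also stands. The gap is in event-level reporting to the ethics committee, the Sponsor and the TSC; related events are not hidden altogether.

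Finally, suicide risk has its own route at participant level: a letter to the GP at set item responses, and possible clinician follow-up. That route works whatever the relatedness judgement. It informs the participant's own care, however, and does not tell the bodies that decide whether the trial should change.

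**Conclusion.** The concern holds. As written, no SAE judged related to the trial meets the criterion for event-level reporting, and every unexpected SAE judged unrelated does. For the TSC and DMEC the fallback is a quarterly report, so a wait of up to about 3 months. For the Research Ethics Committee and the Sponsor the article offers no fallback.

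The conclusion rests on the literal sentence and on the absence of any other route in the article. It makes no assumption about how many SAEs would occur, on which the document gives nothing, and it does not claim that staff acted on the literal wording. That the word is a slip for *related* is the likeliest reading, but the document does not settle it. Because the error is in an operative safety rule, it must be corrected and should not be left for readers to infer.

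**What to change.** Reword the sentence so that serious adverse events that are unexpected and related, or possibly related, to trial participation are reported to the main Research Ethics Committee, the Sponsor and the TSC. The words *possibly related* are a suggestion, so that an uncertain judgement does not remove an event from the rule; the article does not define this category, and the Sponsor should confirm it. Unrelated SAEs stay in the quarterly reports.

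Then:
- check that the adverse event operating procedure, the full protocol and the relatedness field in the database carry the same rule;
- go through the SAEs already on the database and confirm that any judged related reached all three recipients;
- tell the investigators and the Sponsor of the correction.

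The cost is one sentence, a document check and a short notice. Sample size, outcomes, randomisation and analysis are unaffected.

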### Independent oversight

A TSC and Data Monitoring and Ethics Committee will have independent oversight of the study, meeting at 6 monthly intervals with quarterly reports of adverse and serious adverse events.

### Potential limitations

The majority of participants in this study will receive a diagnosis of ASD during adulthood and thus may not be representative of all adults with ASD.

TAU may vary considerably by geographical region and service factors may act as a potential confound.

## Summary

High rates of co-occurring depression, a debilitating mental health problem, have been reported in adults with ASD.^6^ There has been little research to date about the usefulness of adapted CBT for depression in autism or about routine service outcomes for this group. This feasibility study aims to develop a low-intensity intervention for depression for adults with autism based on cognitive-behavioural principles and accompanying therapist guidelines and training. The study design will enable the research team to consider the feasibility of carrying out a large-scale RCT to consider the effectiveness of the intervention, including specifying the most appropriate primary outcome measure. The nested qualitative study will address issues of patient and therapist acceptability of the intervention.

### Trial status

The pilot RCT is currently open to recruitment and the last participant is scheduled to be randomised by the end of September 2017. The trial will run until the end of April 2018.

The full trial protocol can be accessed at NIHR Journals Library (https://www.journalslibrary.nihr.ac.uk/programmes/hta/144302#/).
